### 2.4. Randomization and Blinding

Randomization will be stratified by center and performed using the permuted block technique within each site by a researcher independent of the study. Due to the nature of the intervention, the group allocation cannot be concealed from the participants or the provider of the intervention. Participants will be assigned to one of two conditions within the first week from the baseline assessment (Figure 1).

Moreover, the Standard Progressive Matrices (SPM) [54,55] will be administered. It consists of 60 items measuring nonverbal intelligence divided into 5 sheets (12 items each). Each item requires completion of a series of figures with a missing part that is presented among distractors, according to an increasing difficulty criterion.

Then, the Italian versions of the following neuropsychological tests will be collected pre- and post-treatment and used as the primary outcomes.

The Wisconsin Card Sorting Test (WCST) [56,57] will be used to assess abstract reasoning, mental flexibility, and problem-solving. The examinee has to match stimulus cards to one of four category cards. Cards can be matched by shape (cross, circle, triangle, star), color (red, blue, yellow, green), and number (one, two, three, four). The rule must be worked out by the feedback provided by the examiner (“right” or “wrong” response). When a rule is identified (i.e., 10 consecutive correct matches), the examiner changes the criterion without saying anything, and the examinee has to identify the new rule. Scoring provides the following indices: total mistakes, total correct responses, completed categories, perseverative mistakes, non-perseverative mistakes, percentages of perseverative mistakes, attempts to complete the first category, inability to retain the criterion, and task learning.

The Phonemic/Semantic Alternate Fluency Test [58] will be used to assess the verbal set-shifting ability. The examinee has to produce word pairs unusually, starting from a phonemic cue (letter A, F, S) and a semantic cue (color, animal, fruit), in 60 s. The raw score (number of word pairs obtained for each association (A–color; F–animal; S–fruit)) is adjusted for age, education, and gender; thus, it is converted into an equivalent score. Moreover, a composite shift index evaluating working memory is determined as follows: Total Alternate Fluencies/(Total Phonemic Fluencies + Total Semantic Fluencies/2).

The Trail Making Test (TMT) [59] is a measure of visual processing speed (Part A) and dual-task/cognitive flexibility (Part B). In the first part, the examinee is required to sequentially join a series of numbered circles and, in the second part, to alternate sequences of numbers and sequences of letters by linking the stimuli together (e.g., 1-A → 2-B → 3-C). Scoring is based on the time completion for each part. The raw score is adjusted for age and education; thus, it is converted into an equivalent score.

The Rey–Osterrieth Complex Figure (ROCF-C) [60] is a pen-and-paper task measuring global processing ability. Subjects are required to copy a complex figure (ROCF-C).

A Central Coherence Index (CCI) is derived from the composite score of two independent indices: the order of construction index (order in which the elements of the figure are drawn) and the style index (continuity of drawing). The CCI ranges from 0 (most detailed approach) to 2 (most coherent approach), where higher scores mean a more coherent drawing style [61].

The Test of Attentional Performance (TAP) [62,63] is a computerized battery assessing various attentional domains. The following subtests will be administered.

-Sustained attention (15 min): A series of stimuli are displayed on the screen, and the examinee has to detect the target among the distractors during a prolonged presentation. The stimuli differ in dimension, color, shape, size, and filling.-Cross-modal integration (2 min and 50 s): Participants need to identify the crucial combination of a preceding tone (i.e., high or low) with a subsequent visual stimulus (i.e., an arrow pointing up or down).-Flexibility, from a simple (1 min and 45 s) to a complex (3 min) configuration: This subtest involves a set-shifting task requiring participants to react to complementary target stimuli (e.g., a letter and a number) in an alternating manner.-Inconsistency (3 min): This test examines the sensitivity to interference (i.e., stimulus-response incompatibility). The subject is required to respond with the right or left hand, regardless of the direction signaled by the stimulus.-Working memory (5 min): This test examines the management of information flow and the updating of data by detecting differences in number sequences presented in series.

Each subtest is preceded by a run-in, and the difficulty level of the task may change, according to the examiner’s guide. The TAP subtests are measured by the reaction times and accuracy determined as correct responses, false responses, omissions, and anticipations (i.e., responses within 100 ms).

The Detail and Flexibility Questionnaire (DFlex) [64,65]: A self-report questionnaire consisting of 24 items on a 6-point Likert scale (from 1 = strongly disagree to 6 = strongly agree) and assessing cognitive rigidity (RC, 12 items) and attention to detail (AD, 12 items). The subscale scores range from 12 to 72 and are calculated by summing the RC items and the AD items.

The Cognitive Flexibility Inventory (CFI) [66,67]: A self-report questionnaire consisting of 20 items used to assess two different subscales: the Alternative subscale, which evaluates the ability to perceive multiple alternative explanations for life events and human behavior, and the ability to generate multiple alternative solutions to difficult situations; and the Control subscale, which assesses the tendency to perceive difficult situations as controllable. Each item is scored on a 7-point Likert scale (from 1 = strongly disagree to 7 = strongly agree). The scoring requires inverse scoring of the selected items. The total score is calculated by the sum of all the items. Higher scores indicate greater cognitive adaptability and flexibility to be used in stressful situations; lower scores indicate greater cognitive rigidity associated with less cognitive flexibility in stressful situations.

The Italian versions of the following psychological measures will be also collected pre/post-treatment and used as secondary outcomes.

The Eating Disorder Examination Questionnaire (EDE-Q) [68,69] is a self-report questionnaire consisting of 33 mixed-type items (yes/no, 7-point Likert scales and visual analog scales) assessing the core symptoms of the eating disorder in the past 28 days. The EDE-Q has four subscales (i.e., Restraint, Eating Concern, Shape Concern, and Weight Concern) and a global score is calculated by the mean of all four subscales. Higher scores indicate an elevated frequency or clinical severity of eating disorder symptoms.

The World Health Organization Quality of Life (WHOQOL-BREF) [70]: A self-assessment questionnaire consisting of 26 items rated on a 5-point Likert scale and grouped into four dimensions: physical health (i.e., mobility, daily activities, functional capacity, energy, pain, and sleep), psychological health (i.e., self-image, negative thoughts, positive attitudes, self-esteem, mindset, learning ability, memory concentration, religion, and mental condition), social relationships (i.e., personal relationships, social support, and sex life) and environmental health (i.e., financial resources, safety, health and social services). It also contains QoL and general health items. The score ranges from 25 to 130 and is transformed linearly into a 0–100 scale.

The University of Rhode Island Change Assessment Scale (URICA) [71]: A self-report questionnaire consisting of 28 items rated on a 5-point Likert scale (from 1 = strongly disagree to 5 = strongly agree) representing four primary stages of change in Prochaska and DiClemente’s Trans-Theoretical Model (1982) [71], with 7 items for each of the following subscales: Precontemplation, Contemplation, Action, and Maintenance. To obtain a Readiness to Change total score, the items from each subscale must be summed, then divided by 7 to obtain the mean for each subscale. Following this, the means for the Contemplation, Action, and Maintenance subscales must be summed, and the Precontemplation mean subtracted (C + A + M − PC = Readiness).

Psychodiagnostic and psychological measures will be collected in group settings, in a dedicated room, by clinical psychologists independent of the study. Neuropsychological tests will be administered individually by neuropsychologists independent of the study in appropriate settings.

The duration of the assessment will be two hours for each patient, divided into two sessions (group and individual) on consecutive days.

Personal information will be entered and coded securely with quality control procedures (e.g., double data entry, range checks).

Data will be shared securely in compliance with data protection regulations to maintain participant confidentiality before, during, and after the trial.

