Therefore, the present multicenter randomized controlled trial (RCT) aims to implement and evaluate a personalized CA-CRT program for individuals with AN as an adjunct to standard nutritional rehabilitation (treatment as usual, TAU). The study will test the feasibility and efficacy of CA-CRT in enhancing selected neuropsychological outcomes (cognitive flexibility and central coherence) and psychological measures (eating disorder symptomatology, health-related quality of life, and motivation to change) among inpatients with AN. The feasibility of the study will be evaluated through indices such as the recruitment and retention rates and the patient outcomes. These metrics will help determine not only whether the intervention is acceptable but also whether it can be implemented in routine clinical settings. By delivering a structured, scalable, and individually tailored intervention, the trial seeks to promote more effective, patient-centered care approaches. It is hypothesized that participants allocated to the experimental group will demonstrate greater improvements in the targeted outcomes compared to those receiving standard care alone over the 5-week intervention period. Specifically, the primary hypothesis is that participants in the CA-CRT group will show significantly greater improvement from baseline to post-treatment than those in the TAU group in relation to cognitive flexibility, as measured by the Wisconsin Card Sorting Test (WCST), the Phonemic/Semantic Alternate Fluency Test, the Trail Making Test (TMT), the Test of Attentional Performance (TAP), the Detail and Flexibility Questionnaire (DFlex), and the Cognitive Flexibility Inventory (CFI). Improvements are also expected in the Central Coherence Index (CCI) of the Rey–Osterrieth Complex Figure (ROCF-C).

The secondary hypothesis is that the CA-CRT group will show greater reductions in their eating disorder symptoms (EDE-Q), as well as greater improvements in their quality of life (WHOQOL-BREF) and readiness to change (URICA), compared to those receiving TAU.

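### The printed composite shift index halves only the semantic total, so phonemic fluency counts double with no stated reason; this is very probably a misplaced bracket

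*Protocol article*

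**What the plan says.** Section 2.5 (Measures) introduces a set of tests with the statement that the "neuropsychological tests will be collected pre- and post-treatment and used as the primary outcomes". The Phonemic/Semantic Alternate Fluency Test is one of them. The Introduction also places it under the primary hypothesis, on greater improvement "in relation to cognitive flexibility, as measured by the Wisconsin Card Sorting Test (WCST), the Phonemic/Semantic Alternate Fluency Test" and the other tests listed there.

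Section 2.5 gives the test two kinds of score:

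- **Word-pair score.** The raw score is the "number of word pairs obtained for each association (A–color; F–animal; S–fruit"). It is adjusted for age, education and gender and converted to an equivalent score.
- **Composite index.** The text adds that "a composite shift index evaluating working memory is determined as follows": "Total Alternate Fluencies/(Total Phonemic Fluencies + Total Semantic Fluencies/2"). The closing bracket comes after the 2.

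Section 2.7 (Statistical Analysis) names alternate fluency among the dependent variables of the MANCOVA. It does not say whether the raw, equivalent or composite score enters.

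**The concern.** By ordinary operator precedence the division by 2 applies to the semantic total alone. The index therefore weights the phonemic total 1 and the semantic total 1/2. Nothing in the article explains this. The task itself is symmetric: three letters are paired with three categories, and each pair contributes one word of each kind. A 2 standing beside a sum of two totals is most naturally the divisor of their mean, which would need the bracket to close before the division.

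This is an outcome formula in the Methods, so it may be coded exactly as printed. If the mean was intended, the index would then be too low by an amount that depends on each patient's balance of letter and category fluency. Equal changes in the two fluencies would also move it unequally. In a pre–post comparison, a change in letter fluency would be reflected in the index more strongly than the mean-based version allows.

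**Working it through.** **Inputs.** Let A, P and S be the alternate, phonemic and semantic totals named in the section 2.5 formula, and let r = S/P. The article gives no worked value, range or typical totals, so there is no printed figure to reproduce. All values of A, P, S and r below are assumptions for illustration.

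**Step 1: the two readings.**

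- As printed: I₁ = A/(P + S/2)
- Mean of the two totals: I₂ = A/[(P + S)/2] = 2A/(P + S)

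**Step 2: their ratio.**

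I₁/I₂ = (P + S)/(2P + S) = (1 + r)/(2 + r)

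| r = S/P (assumed) | I₁/I₂ |
|---|---|
| 0.5 | 1.5/2.5 = 0.60 |
| 1 | 2/3 = 0.67 |
| 1.5 | 2.5/3.5 = 0.71 |
| 2 | 3/4 = 0.75 |

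Over this range the printed index is 25% to 40% lower. The factor contains r, so it changes between patients and, within a patient, between visits if the balance of the two totals shifts.

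**Step 3: same mean, different index.** Take A = 30.

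- P = 30, S = 45: I₁ = 30/52.5 = 0.571 and I₂ = 30/37.5 = 0.800
- P = 45, S = 30: I₁ = 30/60 = 0.500 and I₂ = 30/37.5 = 0.800

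The mean-based index treats these patients alike. The printed one separates them.

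**Step 4: response to change.** Start from A = 30, P = 36, S = 45, so I₁ = 30/58.5 = 0.513 and I₂ = 30/40.5 = 0.741.

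- P rises by 6: I₁ = 30/64.5 = 0.465 (−9.3%)
- S rises by 6: I₁ = 30/61.5 = 0.488 (−4.9%)
- Either rises by 6: I₂ = 30/43.5 = 0.690 (−6.9%)

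**Step 5: a simple anchor.** If A = P = S, then I₂ = 1 and I₁ = 1/1.5 = 0.67. Only the mean-based form gives 1 when alternating output equals both single-cue totals. This supports the misplaced-bracket reading but does not prove it.

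**The case against.** The strongest reply is that the article contains no second version of the formula, range or worked value that contradicts the printed one, and the scoring source it cites for the test is not at hand. This stands as a limit: the mean is an inference, so the formula must be confirmed before it is replaced. It does not remove the point, because the unequal weights would still need a reason.

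A second reply is that much of the difference may be a common rescaling, which leaves a group-by-time F test and partial eta-squared unchanged. This stands in part. For three assumed sets of totals with r between 1.25 and 1.5, the ratio I₁/I₂ runs only from 0.692 (81/117) through 0.700 (70/100) to 0.714 (75/105). If patients are alike in r, the practical effect is small. The article gives no information on the spread of r. Nor does the mean-based index remove the influence of letter fluency: with P = 36 and S = 45, one extra phonemic word lowers it by about 1.2%, against 1.7% for the printed index.

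A reader might also infer more than the article supports:

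- **That the index cannot be computed.** The only task described is the alternating one ("The examinee has to produce word pairs unusually, starting from a phonemic cue (letter A, F, S) and a semantic cue (color, animal, fruit), in" one minute), and no separate phonemic or semantic trials are listed. But the formula names both totals as inputs, and a condensed article commonly leaves the administration of a cited test to the manual or full protocol. Their absence does not show that the totals will not be collected.
- **That the primary analysis is wrong.** The adjusted word-pair score does not use the formula, and section 2.7 does not say that the index is the score analysed.
- **That centers will produce values that cannot be pooled.** Nothing says that centers score the index separately or by different formulas, and section 2.7 assigns the analysis to one statistician.
- **That the construct is contradictory.** The test as a whole "will be used to assess the verbal set-shifting ability", while the derived index is tied to working memory. These labels attach to different objects, so this is loose wording at most.

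**Conclusion.** The point holds as a defect in a stated scoring formula. As printed, the index halves only the semantic total and gives no reason. A misplaced bracket is by far the most natural reading. If the mean was intended, coding the printed text gives an index 0.60 to 0.75 times the intended one for an assumed r of 0.5 to 2, with a factor that varies by patient and visit.

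The conclusion rests on the literal order of operations, which is certain, and on the inference that the mean was intended, which the article does not confirm. The practical effect depends on the spread of r in the sample and on whether the index enters the analysis. The article gives neither, so an effect on the primary result is possible but not shown.

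**What to change.** Before any scoring, check the formula against the scoring source cited for the test. If it confirms the mean, print the index as A/[(P + S)/2], with the bracket enclosing the sum before the division. If it confirms the unequal weights, keep the formula, write it with explicit brackets as A/[P + (S/2)], and give the reason in a sentence.

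The cost is one check and a one-line text edit, with matching code. The edit itself requires no change to the assessments, the sample size or the word-pair score.

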### 2.3. Sample Size Calculation

The minimum sample size required for this study has been computed using an *a priori* sample size calculator (G*Power 3.1.9.2 software) for the *F* tests [46,47,48]. Participants will be randomly allocated into two groups: (A) TAU plus CA-CRT condition (experimental group) and (B) TAU-only condition (control group). Moreover, the recruits will be assessed before and after the intervention (i.e., 5 weeks). The Pillai V has been set *a priori* to take a value of 0.2, with an effect size of 0.5. Moreover, the type I error (*α*) rate has been set at 0.05 (two-sided), and the power (1 − *β*) at 0.95, respectively. The results showed that there is a 95% chance of correctly rejecting the null hypothesis of no significant interaction effect, with 54 recruits in total (27 per group) for each center.

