### 2.7. Statistical Analysis

Statistical analyses will be performed using SPSS version. 24.0 [73]. Descriptive analyses will be conducted on the experimental group and control group. After preliminary statistical assumption satisfaction, an independent samples T-test will be used to determine whether the groups differ in the psychodiagnostic measures administered at baseline. These potential differences will be used as covariates in the model. A multivariate analysis of covariance (MANCOVA) will then be conducted (factors: experimental group, control group, time; dependent variables: scores obtained in the neuropsychological and psychological measures; covariates: scores obtained in the psychodiagnostic measures at baseline). We will adopt this design because the dependent variables concerning the executive functions (WCST, alternate fluency, and TMT), as well as visuo-perceptive processing (ROCF-C), are moderately but significantly associated, given their involvement in frontal lobe abilities.

Partial eta-squared will be used to determine the effect size of the intervention. The analysis will be performed by an independent statistician, blinded to the treatment allocation, who will discuss the results with the researchers. Missing data will be handled using appropriate statistical methods to minimize bias and ensure robust results.

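### Two primary pre/post tests (TMT and alternate fluency) are carried through to an undefined equivalent score; if that scale is coarse or capped, it blunts the comparison of change

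*Protocol article*

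**What the plan says.** Section 2.5 of the protocol article introduces the test battery with the statement that these "neuropsychological tests will be collected pre- and post-treatment and used as the primary outcomes". TMT and the alternate fluency test both belong to it.

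- **TMT.** "Scoring is based on the time completion for each part". The next step is: "The raw score is adjusted for age and education; thus, it is converted into an equivalent score". No further score is described.
- **Alternate fluency.** The raw score is the number of word pairs for each association. It "is adjusted for age, education, and gender; thus, it is converted into an equivalent score". The section then adds a second quantity: "Moreover, a composite shift index evaluating working memory is determined as follows". This is a ratio of fluency totals and is not described as converted.

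The primary hypothesis in the Introduction concerns change: "significantly greater improvement from baseline to post-treatment than those in the TAU group in relation to cognitive flexibility". Section 2.7 lists what enters the MANCOVA only as "dependent variables: scores obtained in the neuropsychological and psychological measures".

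Nowhere does the article say how many levels the equivalent score has, where its cut-points lie, or whether it has a top class.

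**The concern.** Demographic correction and conversion serve to place one person against a reference population. The trial asks something else: whether one arm improves more than the other over five weeks. Within a patient, age, education and gender are practically the same at both visits, and between arms randomization balances them in expectation. If the adjustment is additive, it cancels from the change score. The conversion therefore offers little to this comparison.

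It may also do harm. Completion time is continuous and a word-pair count is fine-grained. If the equivalent score groups them into a few ordered classes, a patient who improves within a class shows no change. If the top class is open-ended, a patient who starts there cannot show a gain. Section 2.2 requires a diagnosis of anorexia nervosa but no minimum cognitive deficit, so nothing in the entry criteria keeps patients away from such a ceiling.

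At stake is the sensitivity of two primary tests of flexibility. A null result on either could then partly reflect the scale. A gain on retest in both arms would aggravate this under a cap, because more patients would reach the top class.

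**Working it through.** **1. The plan's own sample size.** Section 2.3 sets Pillai V "to take a value of 0.2, with an effect size of 0.5", alpha 0.05 and power 0.95.

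- f² = V/(1 − V) = 0.2/0.8 = 0.25, so f = 0.5.
- For the group-by-time interaction with 2 groups and 2 times: df1 = 1, df2 = N − 2, noncentrality = N × f².
- N = 54: noncentrality = 54 × 0.25 = 13.5 and power = 0.9501. N = 53 gives 0.946.

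The stated 54 per center (27 per group) reproduces exactly. This point finds no error in it.

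**2. Assumed scale, because the document gives none.** Five ordered classes, 0 to 4, with cuts at normative z = −1.645, −1.097, −0.548 and 0. The top class then holds everyone at or above the norm median.

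**3. Information kept per test, baseline-adjusted comparison.** Further assumptions: retest gain of 0.3 SD in both arms, true effect 0.3-0.5 SD, pre-post correlation 0.6-0.8. Pre and post z-scores are simulated as bivariate normal, with 1,000,000 patients per scenario or arm.

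Information kept = (standardized effect on the banded score / standardized effect on the continuous score)².

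| Baseline mean relative to norm | Information kept | Equivalent patients out of 27 per arm |
|---|---|---|
| at the norm | 0.39-0.54 | 27 × 0.39 = 10.5 to 27 × 0.54 = 14.6 |
| 0.5 SD below | 0.55-0.70 | 27 × 0.55 = 14.9 to 27 × 0.70 = 18.9 |
| 1 SD below | 0.65-0.80 | 27 × 0.65 = 17.6 to 27 × 0.80 = 21.6 |

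A change-score comparison is closer to the planned group-by-time test. Over the same three baselines it keeps 0.24-0.75.

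**4. How much depends on the cap.** Five classes without a ceiling at the norm (cuts at ±0.548 and ±1.645) keep about 0.60-0.82. Ten fine bands keep 0.87-0.95. Coarseness alone therefore costs something, the cap adds to it, and a fine uncapped scale would cost little.

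**5. Power at the plan's own effect.** With two equal groups, f = 0.5 corresponds to 2f = 1.0 SD of change. Change-score t-test, 27 per arm, 20,000 runs per setting, pre-post correlation 0.5 to 0.85, same five capped classes. The continuous score gives about 0.95 in every setting.

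| Baseline mean relative to norm | Power, banded score |
|---|---|
| 1.5 SD below | 0.81-0.91 |
| 1 SD below | 0.82-0.87 |
| 0.5 SD below | 0.75-0.78 |
| at the norm | 0.59-0.60 |
| 0.5 SD above | 0.36-0.38 |

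With baseline at the norm, about 50% of patients start in the top class, and 51-58% of treated patients show no change of class.

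**The case against.** The strongest objection is that the article never calls the equivalent score banded or capped. The number of classes, the cut-points and the ceiling are all assumptions, and the cited scoring sources are not available here. This stands. A reader might infer that the conversion discards within-patient change and cannot register gains above the norm. The document does not support that. Even under the assumed five classes, change is coarsened rather than discarded: power stays at 0.81-0.91 for baselines 1 to 1.5 SD below the norm.

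Second, the article does not say outright which score enters the MANCOVA. Section 2.5 describes instruments, and a full protocol or analysis plan may name the variable. For fluency, the unconverted shift index may preserve some information. This stands in part. The index is described as a working-memory measure, so it does not clearly replace the word-pair count as the set-shifting outcome. For TMT, conversion is the last step stated. The point therefore concerns a scoring step that the article writes down, not only its silence.

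Third, the lowest figures assume that patients perform at the norm, whereas the Introduction presents weak set-shifting as a core difficulty in anorexia nervosa. That is fair, and it is why a range of baselines is shown. The entry criteria do not settle where patients will start.

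Fourth, the percentages apply to single tests. The planned analysis is multivariate and includes other measures. This also stands: no loss was computed for the overall test, and none should be inferred.

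**Conclusion.** The point holds in conditional form. Two primary outcomes of change are taken through demographic adjustment to an undefined equivalent score, and the analysis section names no other score. The conversion does little for the between-arm comparison and, if the scale is coarse or capped, costs sensitivity.

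The size rests on the assumed five-class scale, retest gain, effect and correlations. With the cap, a baseline-adjusted comparison loses between about a fifth (1 SD below the norm, best case) and about 60% (at the norm, worst case) of the information per test. Without the cap, the loss is about 18-40%. If the scale is fine and uncapped, or if a continuous score is in fact analysed, little or nothing is lost and only the wording needs attention.

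The sample size of 54 per center is not called into question, and the figures do not show that the trial as a whole is underpowered.

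**What to change.** In section 2.5, name the continuous score at both visits as the dependent variable for each test:

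- **TMT:** completion time in seconds, log-transformed if skewed.
- **Alternate fluency:** number of alternate word pairs.

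Either may be raw or demographically adjusted, but the choice should be stated and be the same at both visits. Use equivalent scores only to describe impairment at baseline. Section 2.7 should refer to these named scores.

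The cost is about one sentence per test. No extra data are needed, because the raw scores have to be recorded to derive the equivalent scores.
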